### Ethical Considerations

#### Ethical Approval

This study received ethical approval from multiple institutional review boards. Approval was first obtained from the Faculty Ethics Research Committee, UiTM on November 7, 2024 (REC/11/2024 [PG/MR/549]). The study was subsequently approved by the Medical Research and Ethics Committee, Ministry of Health Malaysia, on December 16, 2024 (24‐03494-W6I [IIR]), in accordance with the ethical standards of the National Institutes of Health Malaysia. Additional approval was granted by the Medical Research Ethics Committee, UMMC, on May 21, 2025 (2025122‐14637).

Operational approvals were obtained from the Directors of Hospital Kuala Lumpur and UMMC for Phase 1 and from the Director of Selangor State Health Department and the Directors of the 4 participating hospitals for Phase 2. Permission to use all study instruments was formally granted by the respective copyright holders and instrument developers.

Before the study begins, all participants will be informed of the study objectives, procedures, and potential risks and benefits and will provide informed consent. Written informed consent will be obtained prior to enrollment. No financial or material compensation will be provided to participants for their participation in this study.

#### Data Management and Security

Participant data will be obtained through both hard-copy questionnaires and electronic forms, then entered into a password-protected database accessible only to authorized research staff. Double data entry and range checks will be performed for key variables to minimize errors. All electronic data will be stored on secure institutional servers with regular backup. Identifiers (names, phone numbers, and identification number) will be stored separately from research data and linked only through a unique study identification code. The *DemensiaKITA* app does not collect or transmit any identifiable health information; it functions as an information and support tool installed locally on participants’ smartphones.

#### Confidentiality

All personal information obtained from participants will be treated as confidential and used solely for research purposes. Identifiable data will not be included in publications or presentations. Hard-copy documents will be stored in locked cabinets within restricted-access offices. Electronic data will be deidentified for analysis, and only the principal investigator and authorized team members will have access to the code key. Research procedures will comply with the Malaysian Personal Data Protection Act and institutional data protection policies.

#### Data Sharing and Availability

Deidentified individual participant data underlying the main trial results may be made available upon reasonable request to the corresponding author after publication of the primary findings, subject to institutional data-sharing policies and approval by the ethics committees.

### Dissemination Policy

The results of this trial will be disseminated through peer-reviewed publications, conference presentations, and updates to the ClinicalTrials.gov registry record. A lay summary of the main findings will be prepared in Bahasa Malaysia and made available to participating clinics and interested caregivers.

## Results

### Phase 1: Questionnaire Adaptation, Translation, and Validation

This phase focuses on adapting, translating, and validating the questionnaires on KAP and burden level. The following outcomes are anticipated.

#### Content Validation

Content validation will be assessed using the CVI and content validity ratio. To ensure rigorous content validation, an item-level CVI of 0.79 or higher is required for item retention, while a scale-level CVI of 0.80 or higher is necessary to establish excellent content validity for the overall scale. A minimum content validity ratio of 0.99 is established based on expert consultation. This rigorous approach ensures that only the most relevant and important items are retained for subsequent phases of instrument development [29-31,34].

#### Face Validation

Face validation will be assessed by calculating the face validity index (FVI) to quantify the degree of agreement among respondents regarding the clarity and comprehensibility of the questionnaire items. A sample of 30 respondents was used for this process. Items with an item-level FVI and scale-level FVI of 0.80 or higher were retained. This threshold aligns with recommendations for establishing strong face validity [33-35].

#### Construct Validation

Construct validation will be conducted using EFA to identify the underlying factor structure of the questionnaire. This will confirm that the items are effectively measuring the intended concepts. Additionally, correlational analysis will examine the relationships between different scales within the questionnaire to assess convergent and discriminant validity [34,36,45].

#### Reliability

To ensure the questionnaire’s consistency, 2 key aspects of reliability will be evaluated. First, internal consistency will be assessed using Cronbach α, which measures how well the items within the questionnaire work together to measure the same concept. A Cronbach α of .70 or higher will be considered acceptable. Second, test-retest reliability will be assessed using the intraclass correlation coefficient. This determines the stability of the questionnaire’s results over time, with an acceptable value of 0.75 or higher [34,39,41]. This 2-pronged approach ensures the questionnaire produces reliable and consistent results.

### Phase 2: Intervention Effectiveness and Data Analysis

This phase focuses on evaluating the effectiveness of the *DemensiaKITA* mHealth app compared to the usual care.

#### Inferential and Longitudinal Analysis

All analyses will be conducted using a 2-sided significance level of *α*=.05. Descriptive statistics will summarize sociodemographic and caregiving characteristics by study arm [46]. Categorical variables will be presented as frequencies and percentages, and continuous variables as means and SDs or medians and IQRs, as appropriate. Baseline comparability between the intervention and control groups will be examined using chi-square tests for categorical variables and independent *t* tests (or nonparametric equivalents) for continuous variables [46,47].

The primary effectiveness analysis will use generalized estimating equations models to compare changes in knowledge, attitude, practice, and burden scores between the intervention and control groups over time (baseline, 1 mo, and 3 mo). For each outcome, a GEE model with an appropriate link function and working correlation structure will be fitted, including fixed effects for group (intervention vs control), time, and the group-by-time interaction. The group-by-time interaction term will be interpreted as the main estimate of the intervention effect. To account for potential confounding due to nonrandom allocation, the models will adjust for prespecified baseline covariates (age, sex, and relationship with the people living with dementia, caregiving duration, and baseline score of the corresponding outcome). Robust standard errors will be reported [21,48].

Effect sizes (Cohen *d* for between-group differences in mean change) will be calculated to quantify the magnitude of the intervention effect, in addition to *P* values and 95% CIs [21,48].

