**Methods:**

This research will be conducted in 2 phases. Phase 1 involves the adaptation, translation, and validation of 4 instruments: Dementia Knowledge Assessment Tool Version 2, Dementia Attitudes Scale, Caregiver Task Inventory—25 items, and Short-form Zarit Burden Interview—12 items. Content, face, and construct validity, along with reliability (Cronbach α and test-retest intraclass correlation), will be established. Phase 2 is a single-blinded NRCT conducted in 4 public hospitals. A total of 100 caregivers will be recruited. Two intervention hospitals will receive the *DemensiaKITA* app, while 2 control hospitals will receive usual care (Ministry of Health dementia leaflets and video). The primary outcomes (KAP) and secondary outcome (burden level) will be assessed at baseline, 1 month, and 3 months using the validated questionnaires on an intention-to-treat basis. Data will be analyzed with descriptive statistics, chi-square and *t* tests, and generalized estimating equations.

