### Phase 2: Effectiveness of the *DemensiaKITA* mHealth App

#### Overview

In Phase 2, the research assesses the effectiveness of the *DemensiaKITA* mHealth app intervention among dementia caregivers in Selangor, Malaysia. This phase uses an NRCT with 2 parallel arms (intervention and control) and a 1:1 allocation ratio. The study includes 3 assessment points: baseline (T0), 1 month (T1), and 3 months (T2). The intervention period spans from August 2025 to February 2026. Participants will be blinded to group allocation (single-blinded). Hospital-level allocation is applied to minimize contamination (Figure 2). Eligibility criteria for Phase 2 are given in Textbox 2.

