### Sample Size Calculation

The sample size for Phase 2 was calculated for comparison of 2 independent means (intervention vs control) assuming equal group sizes, a 2-sided test with a significance level of *α*=.05, and power (1−β)=0.80. The calculation followed the method described by Rosner [43] and Turnbull et al [44]. The required sample size per group was obtained using the formula:

$$n=\frac{(\sigma_{1}^{2}+\sigma_{2}^{2})(Z_{1-\alpha /2}+Z_{1-\beta }{)}^{2}}{\Delta^{2}}$$

where $\sigma_{1}$ and $\sigma_{2}$ are the SDs in the 2 groups, $Z_{1-\alpha /2}$ is the standard normal deviate at the 5% (1.96) significance level, $Z_{1-\beta }$ is the standard normal deviate for 80% (0.84) power, and Δ is the expected mean difference between the groups.

Based on Turnbull et al [44], an expected mean difference in knowledge scores of 1.69 was used, with SDs of 2.53 and 2.76, respectively. Substituting these values:

$$n=\frac{(2.53^{2}+2.76^{2})(1.96+0.842{)}^{2}}{1.69^{2}}\approx 38.5$$

Thus, approximately 39 participants are required per group. To account for an anticipated 30% attrition rate, the sample size was inflated:

$$n_{\text{adjusted}}=38.5\times 1.30\approx 50$$

Accordingly, 50 participants will be recruited into each arm (intervention and control), giving a total sample size of 100 caregivers.

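### Three primary outcomes are each tested at an undivided two-sided 0.05 with no hierarchy or success rule, and power is calculated for knowledge only

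*Protocol article*

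**What the plan says.** The Abstract (Methods) ranks the outcomes: "The primary outcomes (KAP) and secondary outcome (burden level) will be assessed at baseline, 1 month, and 3 months". Knowledge, attitudes and practices are therefore three primary outcomes, and burden is secondary.

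Inferential and Longitudinal Analysis opens with the error rule: "All analyses will be conducted using a 2-sided significance level of" .05. It then describes the main effectiveness model, used "to compare changes in knowledge, attitude, practice, and burden scores between the intervention and control groups over time". Each score has its own model: "For each outcome, a GEE model with an appropriate link function and working correlation structure will be fitted". The effect of interest is defined in the singular: "The group-by-time interaction term will be interpreted as the main estimate of the intervention effect". Time has three levels in that model (baseline, 1 month, 3 months).

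Sample Size Calculation uses one outcome only: "an expected mean difference in knowledge scores of 1.69 was used", with SDs of 2.53 and 2.76, two-sided alpha 0.05 and 80% power. It names no time point.

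The Abstract (Results) expects significant improvement in all three KAP outcomes and lower burden. It does not say how a mixed result would be read.

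**The concern.** A level of 0.05 per test protects each outcome taken alone. It does not hold 5% across a family of three primary outcomes unless a rule connects them, such as a fixed order, a split of alpha or a requirement that all succeed. The article states the 0.05 level for all analyses and gives no such rule. If one of three primaries reached significance, nothing in the text would prevent the app from being reported as effective, and the error rate of that claim would exceed 5%.

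Two further points follow from the same passages:

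- No power is stated for attitude or practice, although both are primary. This is a question of power and does not affect the false-positive rate.
- Burden appears alongside the primaries in the main effectiveness model. The analysis section should make clear that it remains secondary, as in the Abstract.

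**Working it through.** **Inputs from the article**
- Primary outcomes: 3 (Abstract, Methods).
- Level: two-sided 0.05 for every analysis (Inferential and Longitudinal Analysis).
- Follow-up times: 1 and 3 months.
- Sizing: difference 1.69, SDs 2.53 and 2.76, power 0.80, 30% attrition (Sample Size Calculation).

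**1. The plan's own figure**
- n = (2.53² + 2.76²)(1.96 + 0.842)² / 1.69² = 14.0185 × 7.8512 / 2.8561 = 38.54, so 39 per group.
- 38.54 × 1.30 = 50.1, so 50 per arm.

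The figure reproduces. It covers one knowledge test with the whole 0.05.

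**2. Any-win error with one test per primary outcome**

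Independent tests: 1 − 0.95³ = 14.3%.

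The article gives no correlations between outcomes, so a range is assumed. These values come from 500,000 simulated draws with one normal test statistic per outcome.

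| Assumed outcome correlation | At least one false positive among 3 |
|---|---|
| 0.3 | 13.7% |
| 0.5 | 12.5% |
| 0.7 | 11.0% |

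**3. Counting only false results in the app's favour**

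Each two-sided test carries 2.5% in that direction. For three independent tests, 1 − 0.975³ = 7.3%, against a nominal 2.5%. This applies to single-contrast tests, because a joint test of two coefficients has no direction.

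**4. If 1 and 3 months are tested separately**

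With three time levels the group-by-time interaction has two coefficients per outcome, which gives six tests.
- Independent: 1 − 0.95⁶ = 26.5%.
- Outcome correlation 0.3 to 0.7 and between-time correlation 0.5 or 0.7 (all assumed): 17.7% to 23.7%.
- In the app's favour only, independent: 1 − 0.975⁶ = 14.1%.

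**5. What an equal split of alpha would cost**

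Bonferroni over three gives 0.05/3 = 0.0167 per outcome.
- Knowledge then needs 52 evaluable per group instead of 39. Allowing for 30% loss, 52/0.70 = 74.3, so 75 per arm.
- With 39 evaluable per group, power for knowledge falls from 80.5% to 66.5%.
- With 35 evaluable (50 less 30%), it falls from 76.1% to 60.9%.

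**The case against.** **No any-win rule is written.** This is the strongest objection. The stated aim is to improve KAP and reduce burden together. If all three primaries had to succeed, the type I error would be at most 5%. If each outcome were reported as its own separate claim, each test would keep its 5%. The objection stands to this extent: the inflation depends on how the results are used. The article does not commit to either protective rule, so neither can be relied on. An all-must-succeed rule would also leave overall power unknown, because only knowledge is sized.

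**Multiplicity procedures are often left to the SAP.** A missing procedure alone would not be a finding here. But the article states a rule, 0.05 for all analyses, and applies it to three outcomes it calls primary. An SAP that controlled the family-wise error would have to depart from that published rule.

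**Stronger readings the documents do not support**
- *Six primary tests as a settled fact.* The article speaks of one interaction term per outcome, and a joint two-degree-of-freedom test fits that wording. The term is also called an estimate, which a joint test does not supply. The text is ambiguous, so 26.5% is conditional.
- *Burden as a fourth primary.* A reader might infer this from its place in the main effectiveness analysis. That label more naturally names the model, and the Abstract calls burden secondary.
- *14.3% as the risk of wrongly favouring the app.* That figure counts errors in both directions. The favourable-direction figure is 7.3%, against 2.5%.
- *Sizing on knowledge as a cause of false positives.* It is not one. Nor would null results on attitude or practice be unreadable, since 95% CIs and Cohen d are planned.

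**Conclusion.** The concern holds in limited form. The article applies an undivided 0.05 to each of three primary outcomes and gives no rule that connects them. If success on any one supports effectiveness, the two-sided family-wise error is up to 14.3%, roughly two to three times nominal across the correlations examined. The larger 26.5% applies only under separate testing of the two follow-up times.

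These figures assume that each test on its own holds its nominal level, that success on any one primary is enough for a claim, and that the outcome correlations lie in the assumed range. The first is taken as given here, the second is inferred from the absence of a rule, and the third cannot be checked from the article.

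The unstated power for attitude and practice and the unclear placement of burden are separate, smaller matters of reporting.

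**What to change.** Before any analysis, amend the analysis section as follows.

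1. Name one primary contrast per outcome, for example the 3-month group-by-time coefficient, with the 1-month coefficient supportive. The sample size section gives no time point, so 3 months is a choice to be prespecified and does not follow from the sizing.
2. Test knowledge first at two-sided 0.05, since it is the outcome the trial was sized for. Only if it succeeds, test attitude and practice, either in a stated fixed order at 0.05 each or with Holm over the two at 0.05. Either version holds the family-wise error for the three primaries at 5%.
3. State that burden is a secondary outcome analysed with the same model.
4. State that power was calculated for knowledge only.

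This needs no extra participants and leaves knowledge its full alpha, unlike the equal split shown above. Attitude and practice keep primary status. The cost is that neither can support a confirmatory claim if knowledge fails; they would then be reported as estimates with CIs. The Dissemination Policy refers to a registry record, and any entry there would need to match. The Abstract (Results) says data analysis has not begun, so the change can still be made in advance.

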## Methods

### Study Design

This study consists of 2 sequential phases: (1) adaptation, translation, and validation of KAP and burden-related instruments, and (2) evaluation of the *DemensiaKITA* mHealth intervention via a single-blinded NRCT. The NRCT design was selected due to operational and ethical constraints within participating hospitals. Caregivers are tied to specific clinics based on people living with dementia follow-up, and redistributing them across hospitals for randomization would disrupt continuity of care. Cluster randomization was not feasible due to small eligible populations within each site. Individual randomization within the same clinic would introduce high contamination risks, as caregivers frequently interact and could share intervention materials.

To mitigate potential biases inherent in nonrandom allocation, the study incorporates several methodological safeguards: (1) standardized inclusion and exclusion criteria across all sites; (2) selection of hospitals with comparable geriatric services; (3) baseline comparison of groups; and (4) longitudinal analyses using generalized estimating equations (GEE) to adjust for baseline imbalances and repeated measurements [20,21]. This pragmatic design reflects real-world implementation conditions while preserving internal validity.

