It is anticipated that there will be several challenges while conducting this study. Recruiting and retaining participants for both phases of the study, particularly in Phase 2, may be challenging, especially considering the sensitive nature of dementia caregiving and the time commitment required for follow-up assessments. Moreover, adapting and validating the questionnaires into the Malay language requires careful consideration of cultural nuances to ensure the accuracy and relevance of the instruments for the Malaysian population. Additionally, the effectiveness of the *DemensiaKITA* app in improving caregiver KAP and reducing burden levels may be influenced by factors such as individual caregiver characteristics, the severity of dementia in the care recipient, and access to technology and support. Besides that, data collection and analysis can be time-consuming and resource-intensive, requiring careful planning and execution to ensure the accuracy and reliability of the results.

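### As written, the planned covariate adjustment drops out of the group-by-time term, so the main estimate is not adjusted for covariates that affect change

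*Protocol article*

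**What the plan says.** The Inferential and Longitudinal Analysis section of the protocol article uses GEE models to compare scores "between the intervention and control groups over time (baseline, 1 mo, and 3 mo"), so the baseline visit (T0) is one of the repeated responses. The model terms are group, time and their interaction, and "The group-by-time interaction term will be interpreted as the main estimate of the intervention effect".

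The same paragraph then says that "the models will adjust for prespecified baseline covariates (age, sex, and relationship with the people living with dementia, caregiving duration, and baseline score"; the score meant is that of whichever outcome is being modelled, and the reason given is confounding from nonrandom allocation. No covariate-by-time term is named. Robust standard errors are planned; the link function and working correlation are left open.

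The Study Design section relies on this model as one of four safeguards against bias from nonrandom allocation: "longitudinal analyses using generalized estimating equations (GEE) to adjust for baseline imbalances and repeated measurements". Hospitals were preassigned, two per arm (Study Settings; Allocation and Blinding), and the Sample Size Calculation section expects 30% attrition.

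**The concern.** The baseline score stands on both sides of the equation: at T0 the model regresses the score on itself. More importantly, all the listed covariates are fixed at baseline. A covariate that enters only as a main effect shifts a participant's fitted score by the same amount at every visit. The main estimate is a contrast of changes between visits, and a constant shift has no influence on a change.

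The adjustment can therefore look thorough in the results table and yet do nothing to the estimate it is meant to protect. If caregivers at the intervention hospitals differ in, say, age or caregiving duration, and these characteristics affect how scores develop over three months, the resulting bias stays in an estimate reported as adjusted. This applies to all four outcomes.

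**Working it through.** **Inputs from the protocol article.** 50 per arm; three visits; planning difference 1.69 with SDs 2.53 and 2.76; 30% attrition (Sample Size Calculation). Model terms and covariates as in the Inferential and Longitudinal Analysis section.

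**1. The plan's own figure.** n = (2.53² + 2.76²)(1.96 + 0.842)² / 1.69² = 14.0185 × 7.851 / 2.856 = 38.5, so 39 per arm; 38.5 × 1.30 = 50. This reproduces and is not in dispute here. It supplies the yardstick of 1.69 points and an average SD of √(14.0185/2) = 2.65.

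**2. Algebra.** Take an identity link, complete data and one working correlation for all participants. Group, time and group-by-time give each group-by-visit cell its own mean. For any covariate coefficients b, the estimating equations give

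fitted mean(g, t) = Ȳ(g, t) − b′X̄(g).

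The second part does not depend on t. Hence

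[fitted(1, t) − fitted(1, T0)] − [fitted(0, t) − fitted(0, T0)] = [Ȳ(1, t) − Ȳ(1, T0)] − [Ȳ(0, t) − Ȳ(0, T0)].

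This is the unadjusted difference in mean change, whatever b is.

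**3. Numerical check.** One simulated data set, 50 per arm, complete data, identity link:

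| Model | T1 (SE) | T2 (SE) |
|---|---|---|
| No covariates | −0.268777 (0.436027) | −0.004009 (0.524205) |
| Planned covariates as main effects | −0.268777 (0.436027) | −0.004009 (0.524205) |

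The match held under independence, exchangeable and unstructured working correlation. With time as a linear term under exchangeable correlation, both models gave 0.017766.

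**4. Bias when a covariate affects change.** Assumed: true effect 0, a covariate imbalanced by 0.5 SD, and 1 point of 3-month change per SD of that covariate. Expected bias is 0.5 × 1 = 0.5 points. Over 200 simulated trials with complete data, the unadjusted and planned estimates both averaged 0.496 (largest difference 8e-16). Neither assumed figure comes from the article, so a range is needed:

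| Imbalance (SD) | Points per SD | Bias (points) | Share of 1.69 |
|---|---|---|---|
| 0.25 | 0.5 | 0.125 | 7% |
| 0.25 | 1 | 0.25 | 15% |
| 0.5 | 1 | 0.50 | 30% |

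**5. When the exact result fails.** With 30% missing completely at random at T2, same assumptions: planned 0.485, unadjusted 0.478. With stronger assumed confounding and about 30% covariate-related dropout, planned 0.94 against unadjusted 0.91 (exchangeable) or 0.85 (independence), truth 0; in single trials the two differed by 0.10 or 0.25 on average, against an SD of about 0.7. With a log link on one complete data set, T2 was 0.0083 against 0.0063. The estimate moves a little; under attrition the bias did not go away.

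**6. What removes it.** In a further simulation with 30% missing at T2, planned and unadjusted both averaged 0.45, truth 0. Crossing the listed confounders with time brought the simulated bias to about −0.04.

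**7. What baseline as a covariate does instead.** Assume no treatment effect, no covariate effect on change, a stable 0.5 SD difference between the arms, SD 2.65 and correlation 0.6 between visits. The change contrast averages 0. A model conditioning on baseline averages (1 − 0.6) × 0.5 × 2.65 = 0.53 points, or 0.27 for a 0.25 SD difference. A simulation of a stable 0.5 SD difference gave 0.59 for that model and about 0.03 for both the planned and the covariate-by-time models.

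**The case against.** **The article never says main effects only.** True. It says the models adjust for the covariates, and a condensed article need not list every term. But it does list the response visits, the fixed effects, the covariates and the estimand term, and the only interaction it names is group-by-time. Main effects are the natural reading, and the point rests on that reading.

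**Perhaps T0 was meant only as a covariate.** The text puts baseline among the compared visits. If T0 were removed from the response, group-by-time would compare 3 months with 1 month, which is not the intervention effect.

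**A reader might infer that the trial has no analytic protection against confounding.** The documents do not support this. The group-by-time contrast is a difference in differences and removes any stable additive difference between the arms, measured or not. The Study Design claim about baseline imbalance is met to that extent.

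**A reader might infer that the estimate is always identical to the unadjusted one.** Exact equality needs an identity link and complete data; the article leaves the link open and expects attrition.

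**A reader might infer that regression to the mean biases the result.** Phase 2 eligibility does not select on any outcome score. If the hospital populations differ, each arm regresses toward its own mean, so only chance imbalance is left.

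**A reader might infer that an essential confounder is missing**, because the Discussion names "the severity of dementia in the care recipient". That sentence says severity may influence how well the app works, alongside caregiver characteristics and access to technology. It describes possible effect modification and does not establish confounding.

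**Conclusion.** The point holds in a limited form. On the natural reading of the article, the baseline score is both response and covariate, and the listed covariates do not adjust the estimate named as the main one. With an identity link and complete data, the estimate and its robust SE equal those of the unadjusted difference in mean change. With attrition or another link they differ slightly, and in the attrition simulations the bias from covariates that predict change remained. The stated adjustment for nonrandom allocation therefore does not do that part of its job, although differencing still deals with stable group differences.

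The size cannot be read from the article. It is the product of an assumed imbalance and an assumed effect on change: 0.5 points at 0.5 SD and 1 point per SD, and proportionally less below that. It is zero if no listed covariate is both imbalanced and related to change.

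**What to change.** Keep T0 as a response. Remove the baseline score from the covariates. Add covariate-by-time terms for age, sex, relationship and caregiving duration. Name the group-by-time contrast at 3 months as the main estimate.

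A model of T1 and T2 with baseline as a covariate, reporting the adjusted group difference at 3 months, can be a sensitivity analysis. It should not replace the main model without comment: with preassigned hospitals it is biased when the arms differ stably at baseline (about 0.5 points in step 7 of the working).

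The cost is a change of wording, a few lines of code and a few parameters: with time categorical, two coefficients each for age, sex and duration (six in all) plus two for each relationship category beyond the reference. The article reports that Phase 2 had not started at submission and that data analysis had not begun, so the change could be made before outcomes are analysed. It controls only the measured covariates; unmeasured influences on change would remain.
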